## Abstract

**Background:**

The COVID-19 pandemic and the protracted lockdowns have heavily impacted university students’ mental health. Digital Escape Games represent a good means to reach students and propose them solutions for their psychological well-being.

**Objective:**

This study aimed to evaluate a cocreated digital Escape Game on students’ mental health in the aftermath of the COVID-19 pandemic, called EscapeCovid Game. The evaluation of the effectiveness of this stand-alone intervention concerns mental health outcomes (mental health literacy, appraisal and change of beliefs about mental health, management of emotions, and development of coping strategies) and the appreciation and relevance of the game.

**Methods:**

A randomized controlled trial with pre- and posttest data collection (online questionnaires with validated scales) is conducted among 500 students in Bordeaux, France, to evaluate the EscapeCovid Game cocreated with students, researchers, health professionals, and web developers. A subsample of students is randomly selected for responding to a semistructured interview following a mixed methods design. Recruitment is done through mail invitations from student associations and presentations in university classes. Half of the sample of the trial plays the Escape Game, while the other half receives an email with mental health–related information. Within the game, students discuss their personal experiences. The text is further used for the qualitative analyses. The whole study is carried out online.

**Results:**

The EscapeCovid Game has been developed, tested, and finalized by the end of March 2023. As of November 4, 2024, a total of 191 students have answered the baseline questionnaire (90 intervention vs 101 control). A total of 23 students have played the game and 53 are in the control arm. Among participants, by the end of September 20, 2023, twenty were interviewed (10 intervention and 10 control) reaching sample saturation. According to preliminary results, the EscapeCovid Game has had a positive impact on all defined outcomes, while the email has been effective in increasing knowledge on resources available and on coping strategies and meditation techniques. We expect the trial to be completed by the end of June 2025.

**Conclusions:**

The mixed methods findings of this study are due to demonstrate the effectiveness of the EscapeCovid Game in improving students’ mental health outcomes. Preliminary results from the qualitative substudy are promising: in the aftermath of the COVID-19 crisis, this intervention is intended to promote players’ mental health through gamification, knowledge transfer, and a learning-by-doing approach.

**Trial Registration:**

ClinicalTrials.gov NCT06720792; https://clinicaltrials.gov/study/NCT06720792

**International Registered Report Identifier (IRRID):**

DERR1-10.2196/64068

## Introduction

### Background

Mental health problems among young people have skyrocketed with the COVID-19 crisis [1]. Repeated lockdowns and curfews between 2020 and 2021 were the causes of a general mental distress well-documented in the literature [2]. These measures had detrimental and long-lasting psychosocial consequences like acute stress and trauma-related disorders, particularly in specific at-risk populations such as students [3].

University students were in fact concerned as a vulnerable population. Independently from the presence of a pandemic, suicide is the second leading cause of death among them and, by the age of 25 years, 75% of those who will have a mental health disorder have had their first onset [4,5]. During the COVID-19 crisis, students were exposed to supplementary heavy stressors: isolation, classes exclusively online, and uncertainty about their academic and professional future. Several studies have shown how the COVID-19 pandemic and its lockdowns had negatively affected students’ mental health across the world [6,7]. Therefore, it is fundamental to implement mental health promotion and prevention interventions aimed to support students during this crisis. Evaluation of these interventions is a pivotal process in public health research to determine their effectiveness and improve their quality in relation to the targeted population [8].

Among innovative interventions, Escape Games are “live-action team-based games where players discover clues, and solve puzzles [...] in order to accomplish a specific goal, usually escaping from the room, in a limited amount of time” [9]. Escape Games are the digital internet-based online version of Escape rooms. Previous research has proved that Escape Games can increase knowledge on health-related topics using the learning-by-doing technique [10]. Furthermore, gamification is based on a learning by making mistakes approach. Related flow theory states that simple simulation can be perceived as more anxiety-provoking than the purely playful approach which integrates error as a dynamic element.

Compared with other interventions, they are supposed to be more attractive and acceptable for a young audience, especially because of their gamification approach. Gamification relies on immersion through which players feel embedded in the game as several psychosocial determinants (eg, social support, environment) are leveraged. In particular, health-related Escape Games use puzzle solving as a strategy to access health promotion and prevention messages. The step-by-step sequencing and the resolution of the enigmas stimulate the learning loop and over-solicit the cognitive capacity of participants (ie, better awareness of the concerned topic, and better capacity to deconstruct one’s beliefs).

Escape Games can contribute not only to increasing knowledge, but also to behavioral change by providing instruments to act in real-life. For instance, by relying on teamwork, participants can develop the notion of mutual support which could be transposed to their communities. Thus, individual and collective behaviors are at stake. The positive outcomes of Escape Games are boosted by their digitalization: through the internet, Escape Games can reach a larger audience with no time or space limit. This should be even more promising in a period where face-to-face contact is very limited. Success of these interventions can also be fostered if they are cocreated with the target population through a design thinking approach (ie, understanding of users’ experience and needs, brainstorming sessions with several stakeholders, and testing of the tool). Cocreation is a collaborative approach offering various benefits such as enriched insight into problems and increased feasibility and acceptability [11]. We applied this approach to produce the EscapeCovid Game, a stand-alone intervention to promote mental health and prevent psychological diseases among university students in the era of COVID-19.

### The EscapeCovid Game

The EscapeCovid Game is focused on four main outcomes: (1) mental health literacy (knowledge of the concept of mental health, from illnesses to psychological well-being), (2) appraisal and change of beliefs about mental health (destigmatization), (3) management of emotions (their recognition and regulation), and (4) development of coping strategies (building resilience). It addresses specifically anxiety and depression whose symptoms were exacerbated by the COVID-19 crisis including the measures undertaken to limit the spread of the virus (eg, repeated lockdowns and curfews, University closure).

The underpinning theories of the game are the COM-B model of behavior (capability, opportunity, and motivation to change behavior) [12], the Plutchik’s wheel of emotions (visualization of emotions to change behavior) [13], and the Transtheoretical model of behavior change (stages of change, processes of change, levels of change, self-efficacy, and decisional balance [14]).

The EscapeCovid Game takes place in Thomas’ apartment which he shares with another student, Hana. Thomas is a university student and we follow him during a typical day in lockdown. To move from one room to another, players must solve all the puzzles by clicking on the objects spread out in Thomas’ room. At the end of each room scenario, a set of cards is shown, with each card containing a mental health-related message. The cards synthesize the messages transmitted through the puzzles in the room.

The game can be played in groups of 4 players who help each other and discuss using their computer cameras and headphones. All along the game, they are helped by a game guide who explains the rules and answers any questions. The same guide concludes the game session with a final debrief where all participants share their experiences.

The EscapeCovid Game has been cocreated jointly by a team of researchers at the University of Bordeaux and a start-up specialized in the production of both physical and digital Escape Rooms, Tricky, in France. We used the PRODUCES (Problem, Objective, Design, End Users, Cocreators, Evaluation, and Scalability) framework [15] composed of 3 steps. First, we tested the hypothesis that the game was effective in promoting the four mental health-related outcomes. Second, we accumulated evidence on the good functioning of the game. Third, we leveraged the right behavior change mechanisms.

Within this framework, the game was cocreated in particular by 1 project manager from a public health research center, 1 student intern completing a degree in cognitive engineering, 1 game designer, 1 developer specialized in computer science, 1 medical doctor, and 1 psychology researcher. Supplementary data to improve the game was provided by 45 questionnaires on the appreciation and relevance of the game by student players, and qualitative semistructured interviews with 10 students of the same sample. The cocreation of the game is detailed in an article by Labrosse et al [16].

### Objective and Hypotheses

The objective of this study is to evaluate among a population of university students the effectiveness of the EscapeCOVID Game on 4 mental health outcomes: mental health literacy, appraisal and change of beliefs about mental health, management of emotions, and development of coping strategies. The appreciation and relevance of the game are also considered in the overall evaluation of the game. This stand-alone intervention is implemented in the era of the COVID-19 pandemic.

Consequential research hypotheses of the study are (1) compared with a group receiving another classical intervention, after playing the digital Escape Game and having received a debriefing, students remarkably improve their mental health literacy, appraisal, and change of beliefs about mental health, management of emotions, and development of coping strategies; and (2) cocreation enhances appreciation and relevance of the digital Escape Game among university students.

The objective of this study is original since, to the best of our knowledge, no Escape Game on students’ mental health outcomes has been developed before following a cocreation approach and evaluated through mixed-methods to prove its effectiveness.

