#### Internet-Based Interviews

There are two sources of qualitative data: (1) semistructured interviews after the intervention with students from both arms and (2) open discussion with the game guide at the end of the game session. Concerning the first source of qualitative data, 20 students were randomly selected among the 2 groups (10 for the intervention arm, and 10 for the control arm) to respond to a semistructured interview. For the discussion embedded in the game, the text produced during the debrief is recorded and analyzed so that the developers of the start-up can work on an algorithm for building a chatbot messenger capable of providing tailored advice to gamers, replacing the game guide. Machine learning will be used for this purpose. In terms of simplicity and feasibility, the sample is recruited on the sole criterion of sex, 50% of girls, through sample saturation. The interviews have been conducted remotely by a public health researcher through an internet-based interview tool. Students are recommended to make the interview at home.

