## Results

### Key Dates of the Study

The study received funding by the French National Research Agency in January 2022. The production of the EscapeCovid Game ended in March 2023. The cocreation process, the test, and the refinement of the intervention lasted 15 months. For the evaluation of the finalized game, the collection and analyses of qualitative data through semistructured interviews has been completed by September 2023. The end of the evaluation phase through the RCT is scheduled to be completed by the end of June 2025. The results of the mixed methods analyses are expected to be published by the end of December 2025. The timeline of the study is illustrated in Figure 1.

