### Study Population

The recruitment started in December 2023.

As of November 4, 2024, a total of 191 students have answered the baseline questionnaire and have been randomly assigned to one of the 2 arms, 90 intervention versus 101 control. A total of 23 students have played the EscapeCovid Game (intervention arm) and 53 are in the control arm. Specifically, 54% (103/191) of the participants at the baseline are students in health care disciplines; 11.5% (22/191) in sciences and technologies; and the remaining participants study other subjects 34.5% (66/191) including psychology, law, and so on.

Concerning qualitative data, 20 students (10 for each arm) have been interviewed on the appreciation, relevance, and acceptability of either the game or the email. Students of the game arm were between 18 and 28 years of age. There were 9 females and 1 male. Their year of study ranged from the first year of their bachelor’s degree to the first year of their doctoral studies. Fields of study included medicine, chemistry, physics, biology, sociology, speech therapy, and political science. Students of the control arm were between 18 years and 28 years old. Their year of study ranged from the second year of their Bachelor’s to the third year of their doctoral studies. Fields of study included medicine, physics, nursing and marketing.

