Not particularly, I don’t think so, it was more focused on knowing emotions rather than how to manage them.Student 1-Male

In comparison to the game, the informative email was not an immersive experience and was not expected to influence students’ cognition, affect, potential, and health behavior. However, it provided useful tips to students from the control arm, including the following: a list of existing sources in case of mental health distress (eg, helplines and free-of-charge consultations with a psychology based at the University of Bordeaux); breathing techniques and meditation; and mental health problems explained with accessible but accurate terminology.

It gave me knowledge I didn't have, about the numbers to contact in case of need [...] we can't know them all by heart and I think that having them all written down in an email or in a document, well I think that it can help us because not everyone knows where to refer and where to go in case of need.Student 1-Male

The usefulness of the email consisted in the fact that it could be used as a memorandum and repertoire of the basics of mental health literacy: knowing that mental health includes both positive mental health and the absence of a mental health problem; knowing the signs of the most common mental health problems (depression, anxiety, and stress); recognizing and managing emotions; learning coping strategies; and having a list of the most known services in case of a mental health distress.

As of November 4, 2024, data from the game debriefs is not transcribed and cannot be analyzed.

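### Hypothesis 2 credits cocreation, but no arm varies it; separately, the interview dates, the sex labels and the abstract's impact claim need reconciling or rewording

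*Protocol article*

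**What the plan says.** **Hypothesis and arms.** Objective and Hypotheses (Protocol article) states as the second hypothesis that "cocreation enhances appreciation and relevance of the digital Escape Game among university students". The Randomized Controlled Trial section describes two arms: one plays the EscapeCovid Game, the other receives an email of tips and resources. Data Collection Tools adds satisfaction items to the second questionnaire, about the game in one arm and the email in the other. It also says that the interviews mainly assess how far the game is appreciated and relevant, and that interviewees discuss the cocreation approach.

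**Interviews.** Internet-Based Interviews says that "20 students were randomly selected among the 2 groups (10 for the intervention arm, and 10 for the control arm". The abstract's Methods and Results likewise present the interviewees as a random subsample of the study's participants. Mixed Methods Research Design says that both kinds of data are gathered at the same time.

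**Dates.** Key Dates of the Study says that "the collection and analyses of qualitative data through semistructured interviews has been completed by September 2023"; the abstract gives 20 September 2023. Study Population opens with "The recruitment started in December 2023".

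**Results already reported.** The abstract states that "the EscapeCovid Game has had a positive impact on all defined outcomes". Of the game-arm interviewees, Study Population says: "There were 9 females and 1 male".

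**The concern.** To claim that cocreation improves appreciation, one must compare something cocreated with something similar that was not. Game versus email changes many things at once: medium, gamification, group play, a live guide and a debrief. A higher rating for the game could come from any of these. Because this is a matter of design, no later analysis plan can repair it. The risk is that good ratings of the game are reported as evidence for cocreation.

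The interview chronology matters for a different reason. The mixed-methods plan uses the qualitative data to explain the effectiveness seen in the trial. If the interviewees came from outside the randomised arms, that explanation rests on other people than those who produced the effect.

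The abstract's wording matters because readers take impact on all outcomes as a finding of effect, and the article says elsewhere that the trial's numbers do not yet allow inference.

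**Working it through.** There is no stated figure to reproduce. The check sets the design against the hypothesis, orders the dates, and compares the abstract with the Results.

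**1. Can the effect of cocreation be identified?**

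| Feature | Game arm | Email arm |
|---|---|---|
| Cocreated game | yes | no game |
| Non-cocreated game | no | no |
| Group play, live guide, debrief | yes | no |
| Tool rated afterwards | game | email |

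Arms that vary cocreation with the game format held fixed: 0 of 2. The satisfaction survey is a second source on appreciation besides the interviews, but its ratings concern different tools, so it cannot isolate cocreation either. Interviewees' views on cocreation are opinions, not a contrast. This conclusion does not depend on when the interviews took place.

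**2. Do the dates fit the sampling description?**

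- Interviews complete: 20 September 2023 (abstract), or at the latest 30 September 2023 (Key Dates of the Study).
- Recruitment start: between 1 and 31 December 2023 (Study Population).
- 20 September to 1 December: 10 + 31 + 30 + 1 = 72 days.
- 20 September to 31 December: 72 + 30 = 102 days.
- Shortest reading, 30 September to 1 December: 31 + 30 + 1 = 62 days.

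On every reading of the stated dates the interviews come first. That cannot be true together with random selection from the two arms and simultaneous collection. Principal Findings repeats September 2023 and treats recruitment for the interviews as a separate and easier task.

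**3. Does the interview evidence cover all outcomes?** Preliminary Quantitative and Qualitative Results gives a favourable quotation for each of the four outcomes. It also reports a player who said that "it was more focused on knowing emotions rather than how to manage them", and students who wanted more coping strategies. The EscapeCovid Game section defines management of emotions as recognition plus regulation, so this player supports the first half and denies the second. The abstract's claim of impact on every outcome is therefore stronger than its source in two ways: it speaks of effect where there is perception, and of all outcomes where one is disputed.

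**4. Do the sex counts agree?** Study Population counts 1 male among 10 game-arm interviewees. The game-arm quotations carry the labels Student 1, Student 5 and Student 7, all male. Three distinct males against one: at least one of the two statements is wrong.

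**The case against.** The strongest reply is that little of the trial is touched. The primary analysis is a between-arm regression that serves Hypothesis 1. No test or decision rule is given for Hypothesis 2, whose evidence is perception-based, so the fault may come down to one causal verb. This is largely right, and it is why rewording suffices. It does not rescue the hypothesis as written.

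Several stronger inferences are tempting but are not supported:

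- *None of the 20 interviewees can belong to the 191 randomised students.* This takes the December date as correct and as referring to trial recruitment. The sentence does not name the trial, although it directly precedes the randomised counts. Other sections say the interviewees were participants, and the timeline figure is not available here. What is established is a conflict, not which side is wrong.
- *The interview sample broke its own sex rule.* The article says "the sample is recruited on the sole criterion of sex, 50% of girls", which describes the sample, not each arm. With 9 females in the game arm, 10 of 20 overall would need 10 − 9 = 1 female among the controls. Their sex split is not given, so a departure is unproven.
- *The abstract contradicts the statement that the trial is too small.* That statement concerns the quantitative data. The abstract's claim follows the interview sentence, and its Conclusions credit the qualitative substudy with the promising results.
- *Hypothesis 2 would be declared supported whatever the truth.* Without a decision rule, this cannot be said.
- *Publishing the claim biases later participants.* The trial is open and self-reported, so this is conceivable, but nothing shows that participants would read or react to the abstract.

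**Conclusion.** The point holds in a limited form. Hypothesis 2 as a causal statement is not identifiable: 0 of 2 arms vary cocreation within a game. This rests only on the described arms and questionnaires and needs no assumption about dates.

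Separately, the stated dates put the interviews 62 to 102 days before recruitment and conflict with the description of the interviewees as a random draw from the arms. If either date is a misprint, the conflict may disappear. If both stand, the interviews are a pre-trial sample.

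The abstract's impact claim exceeds its qualitative basis, though the interviews do legitimately record favourable perceptions. The male count and the student labels disagree, 1 against 3; that is a reporting error with no bearing on whether cocreation can be tested.

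These are corrections that should be made, and they change what the trial may conclude about cocreation. The randomised comparison of game with email on the four mental health outcomes stands apart from all of them.

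**What to change.** 1. Restate Hypothesis 2 as a descriptive aim: estimate appreciation and relevance of the cocreated game among players, with confidence intervals, and make no claim that cocreation caused them.
2. Reconcile the interview completion date, the recruitment start date, the random-selection statements in the abstract and in Internet-Based Interviews, and the simultaneous-collection statement in Mixed Methods Research Design. If a date is wrong, correct it. If the dates stand, describe the interviews as a pre-trial qualitative sample and do not use them to explain the randomised effect as though drawn from its arms.
3. In the abstract, replace the impact claim with wording such as: interviewed players reported perceived benefits, with mixed views on managing emotions.
4. Check the sex counts against the interview records and correct either the count or the student labels. Giving the control arm's sex split would also let readers judge the sampling rule.

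The cost is edits to the abstract, hypotheses, methods and results, plus a check of records. No new arm, participants or analysis are needed. The price is a weaker claim about cocreation and, if the dates stand, a looser link between the interviews and the trial.
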